## Abstract

**Background:**

Chronic obstructive pulmonary disease (COPD) not only affects pulmonary function but also leads to skeletal muscle dysfunction. The various characteristics of different forms of traditional Chinese exercise lead to inconsistent clinical effects in COPD patients. Hence, the present study carefully combined and rearranged *liuzijue*, *wuqinxi*, *baduanjin*, and *yijinjing* into a pulmonary exercise program targeting COPD patients.

**Methods/design:**

This study is a single-blind, randomized controlled trial. A random number table will be generated by an independent person. Each number will be placed in a sealed opaque envelop to blind assignment. All outcome assessors will be blinded to group assignment.

COPD patients between 40 and 80 years of age, with stable medical treatment and no regular participation in regular exercise in the last 6 months will be included. All participants will be recruited from the Respiratory Medicine Department of Yue-Yang Integrative Medicine Hospital Affiliated to Shanghai University of Traditional Chinese Medicine.

All participants will continue to follow their medical treatment. They will be randomly assigned to one of four groups in a 1:1:1:1 ratio: (1) usual care (control group, CG), (2) pulmonary exercise group (PG), (3) resistance exercise group (RG), or (4) combined pulmonary exercise and resistance exercise group (PRG). CG participants will receive medical treatment only. PG participants will perform 60 min of exercise twice a day 7 days a week for 3 months, with 1 day’s exercise per week at hospital under guidance and supervision. RG participants will perform 60 min of resistance exercise once a day, three times a week for 3 months, with 1 day’s exercise per week at hospital under guidance and supervision. PRG participants will perform 60 min of prescribed pulmonary exercise combined with resistance exercise for 3 months.

The outcomes include the isokinetic strength of peripheral skeletal muscle, surface electromyography, 6-min walking distance, 30-s arm curl test, pulmonary function, respiratory muscle strength, dyspnea, body composition, physical activity, quality of life, and Chronic Disease Self-Efficacy Scale.

**Discussion:**

The results of this study will compensate for the current inadequate understanding of prescribed pulmonary exercise and may provide a new, simple, convenient, and effective home-based exercise intervention for COPD patients.

**Trial registration:**

Chinese Clinical Trial Registry, ChiCTR-1800017405. Registered on 28 July 2018.

**Electronic supplementary material:**

The online version of this article (10.1186/s13063-018-3149-7) contains supplementary material, which is available to authorized users.

## Background

Chronic obstructive pulmonary disease (COPD) is a chronic respiratory disease characterized by persistent and progressive airflow limitation, which increases morbidity and mortality. According to statistics reported in *The Lancet*, the morbidity in Chinese people over the age of 40 years has increased from 8.2% in 2008 to 13.7% in 2015 [1], and worldwide mortality from COPD increased by 11.6% in 2015 compared to 1990 [2]. As a systemic disease, COPD not only affects the lungs, causing dyspnea and impaired lung function, but also causes systemic effects including skeletal muscle dysfunction, which further leads to impaired exercise capacity, decreased physical activity, and a poorer quality of life.

Pulmonary rehabilitation (PR) is an important constituent of the non-pharmacological treatment of people with COPD, including but not limited to exercise training, education, and self-behavioral management. It has had significant effects in improving symptoms, exercise capacity, quality of life, and prognosis [3, 4]. Among the diverse methods used in PR, Chinese traditional exercise is a self-healing, functionally integrated aerobic exercise, inducing a possible maximum heart rate of 43–49% predicted [5] and consuming 1.5–2.6 metabolic equivalent units [6]. It is potentially suitable for COPD patients to use at home [7]. The findings from previous studies suggest that Chinese traditional exercise, including tai chi, *liuzijue*, *wuqinxi*, and *yijinjing*, by COPD patients has achieved positive results. Home-based *liuzijue* significantly improved pulmonary function (forced expiratory volume in 1 s [FEV1]), special airway conduction, exercise capacity (measured by the 6-min walking test [6MWT] and 30-s sit-to-stand test), quality of life, and mental health of COPD patients [8, 9]. Moreover, 6 months of home-based (individual) combined with clinic-based (group) *yijinjing* significantly improved pulmonary function (FEV1, FEV1 / forced vital capacity [FVC], and FEV1%pred [FEV1 expressed as a percentage of the predicted value]), exercise capacity (6MWT), quality of life, and emotional regulation in COPD patients [10]. Six months of home-based *baduanjin* significantly improved exercise capacity (6MWT) and quality of life in COPD patients [11]. However, these studies have focused on a single type of traditional Chinese exercise as the intervention, with inconsistent clinical effects on COPD patients according to the exercise type. Moreover, less attention has been paid to the effect of such exercises on skeletal muscle function and physical activity.

Following the basic theory of traditional Chinese medicine, the study combined and reorganized elements from *liuzijue*, *wuqinxi*, *baduanjin*, and *yijinjing* to compile a new intervention of prescribed pulmonary exercise for COPD rehabilitation. The main characteristics of prescribed pulmonary exercise include the “hu” and “si” sounds in *liuzijue*; “pushing up the sky to regulate the triple warmer (meridian)” and “drawing a bow to shoot a vulture” in *baduanjin*; “the crane actions, including the crane spreading its wings and flying” in *wuqinxi*; and “cross-armed iron staff” in *yijinjing* (Fig. 1). Liu et al. [12] demonstrated that rearranged traditional Chinese exercises (including “Wei Tuo offers an iron staff,” form 1 and 2 in *yijinjing*; “pushing up the sky to regulate the triple warmer” and “drawing a bow to shoot a vulture” in *baduanjin*; “si,” “hu,” and “chui” sounds in *liuzijue*; and “the crane actions, including the crane spreading its wings and flying” in *wuqinxi*) improved exercise capacity significantly and induced additional benefits in daily living activity and social participation compared with conventional PR (including pursed-lip breathing and aerobic exercises). Consistent with previous studies, Liu’s study did not examine the effects of exercise on skeletal muscle function and physical activity in COPD patients.

**Fig. 1 Fig1:**
[figure not shown]
Main characteristics of pulmonary exercise. The picture is from the “Teaching video of COPD patient pulmonary exercise” self-recorded by the research group. The teacher in the video is [name], a member of the research group. (a) Rise-up position. (b) “hu” sound. (c) “si” sound. (d) Pushing up the sky to regulate the triple warmer. (e) Drawing a bow to shoot a vulture. (f) Crane actions, including the crane spreading its wings and flying. (g) Cross-armed iron staff. (h) Restore position

However, skeletal muscle dysfunction as a significant extrapulmonary effect of COPD may occur before respiratory symptoms, affecting exercise capacity, physical activity, and quality of life, and is an independent risk factor for predicting mortality in COPD patients [13, 14]. Moreover, exercise limitations in COPD patients may be mainly due to peripheral factors rather than ventilation limitation, and the correlation between lung capacity and exercise capacity is poor [15, 16]. Hence, skeletal muscle function has become an important target for improving the exercise capacity and quality of life of COPD patients and has received increasing attention from clinical and scientific researchers. As an important method for counterbalancing skeletal muscle dysfunction, resistance exercise has obvious advantages in improving skeletal muscle strength and function of COPD patients [17, 18]. Common methods of providing resistance include weight-lifting (dumbbells), bodyweight-lifting, and using elastic bands.

As an easy-to-use, safe, and affordable item, resistance bands are available to most COPD patients and can be applied for home-based exercises. Previous studies have found that the effects of exercising with resistance bands on improving skeletal muscle strength and quality of life in patients with COPD were similar to those of conventional resistance exercise, with the effects on functional exercise capacity (measured by 6MWT) significantly greater than conventional resistance exercise [19]. Exercising with elastic bands has significant positive effects on the endurance of shoulder joints, the strength and endurance of knee joints (measured by the isokinetic strength test), and functional exercise capacity (assessed by 6MWT and 6-min pegboard and ring test) [20]. In addition, home-based long-term exercise with elastic bands can significantly improve skeletal muscle function of the lower extremities (assessed by the isokinetic strength test) and exercise capacity (6MWT and five repetitions of the sit-to-stand test) in COPD patients, and the effects on improving muscle strength (isokinetic peak torque divided by body weight) were more significant than conventional PR [21]. Another study similarly found that home-based long-term exercise with elastic bands can significantly improve the extensor strength of knee joints (assessed by hand-held dynamometry) [22]. Hence, exercising with elastic bands has a wide potential in home-based rehabilitation programs for COPD patients for improving skeletal muscle function and exercise capacity. However, the effects of exercising with resistance bands and the role of prescribed pulmonary exercise on improving skeletal muscle function in COPD patients is unclear, as is whether prescribed pulmonary exercise combined with exercising with elastic bands can achieve additional benefits compared with a single mode of exercise.

Hence, in this study, 3 months of (1) usual care, (2) prescribed pulmonary exercise, (3) exercising with resistance bands, and (4) prescribed pulmonary exercise combined with exercising with elastic bands will be applied as interventions to COPD patients to evaluate the overall effect of prescribed pulmonary exercise on lung function, exercise capacity, skeletal muscle function, quality of life, and psychological function in patients with COPD. The aim of the study is to further clarify the role of prescribed pulmonary exercise in COPD rehabilitation, since it is a simple, fun, easy to learn, operational, and effective intervention for COPD patients. We hypothesize that prescribed pulmonary exercise can significantly improve pulmonary function, exercise capacity, skeletal muscle function, quality of life, and psychological function, and that combined exercise induces additional benefits in COPD patients compared with single exercise methods.

## Methods/design

### Design

This is a single-blind, randomized controlled clinical trial, to investigate the effects of prescribed pulmonary exercise in COPD patients by comparing the effects of (1) usual care, (2) prescribed pulmonary exercise, (3) exercising with elastic bands, and (4) prescribed pulmonary exercise combined with exercising with resistance bands in COPD patients. Participants will be enrolled from the respiratory medicine department of Yue-Yang Integrative Medicine Hospital Affiliated to Shanghai University of Traditional Chinese Medicine. The study protocol has been registered with the Chinese Clinical Trial Registry (ChiCTR-1800017405), and the study has been approved by the Ethics Committee of Yue-Yang Integrative Medicine Hospital Affiliated with Shanghai University of Traditional Chinese Medicine (Shanghai, China). All participants will provide written informed consent to participate in the study.

Participants will be randomly assigned to one of four groups according to a random number table generated by computer, with randomization conducted by an independent person not participating in the recruitment process. Random numbers will be placed in sealed opaque envelopes to blind the group allocation. As exercise interventions will be used in the study, concealing the allocation to the therapist and participants will not be possible, so only the outcome assessors will be blinded with a new evaluator replacing the evaluator familiar with the allocation, to maintain blinding. The study procedure is shown in Fig. 2 and the time points of the study in Fig. 3. The protocol follows the SPIRIT 2013 checklist, provided in Additional file 1.

**Fig. 2 Fig2:**
[figure not shown]
Study flow chart. 6MWT 6-min walking test, CG control group, COPD chronic obstructive pulmonary disease, mMRC Modified Medical Research Council Dyspnea Scale, PASE Physical Activity Scale for the Elderly, PG pulmonary exercise group, PRG pulmonary exercise and resistance exercise group, RG resistance exercise group, sEMG surface electromyography, SES Chronic Disease Self-Efficacy Scale, SGRQ St. George’s Respiratory Questionnaire

**Fig. 3 Fig3:**
[figure not shown]
SPIRIT figure showing time points for enrollment, interventions and assessment. PE pulmonary exercise, RE resistance exercise. *Baseline characteristics include pulmonary function assessed by spirometry, dyspnea assessed by the Modified Medical Research Council Dyspnea Scale, body composition assessed by dual-energy X-ray absorptiometry, and height and weight assessed by a body tester. **Muscle function test includes respiratory muscle strength assessed by spirometry, dominant upper and lower limb muscle strength assessed by a CON-TREX isokinetic dynamometer and by a wireless remote-sensing surface electromyography and analysis system. ***Exercise capacity test includes 30-s arm curl test and 6-min walking test. ****Questionnaire includes St. George’s Respiratory Questionnaire, the Physical Activity Scale for the Elderly, and the Chronic Disease Self-Efficacy Scale

### Sample size

The sample size was based on detecting a minimum difference of 54 m in the 6MWT [11] between the control group (CG) and the pulmonary exercise group (PG) and used a baseline standard deviation of 57 m [11]. With a power of 80% and an alpha of 5% (two-sided), the minimum sample size per group is 18 to give a total of 72 participants. Assuming a drop-out rate of 20%, the minimum sample size in total is 88 (22 participants in each group). The participants will be recruited to achieve a balanced number of patients with different levels of severity of COPD.

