### Statistical analysis

SPSS version 23.0 will be used for data management and statistical analysis. A Kolmogorov–Smirnov test will be used to test for normality, and the normality data will be expressed as mean ± standard deviation, while skewed data will be expressed as median and interquartile range. An intention-to-treat analysis will be used for the allocation, irrespective of whether the participant completes the intervention. Missing outcome data will be handled using a mixed-model method. Then a per-protocol analysis will be conducted, which will include only subjects who completed all outcome measures and followed the intervention protocol. Comparisons of baseline differences between groups will be performed using one-way analysis of variance (ANOVA) or a non-parametric test. Training-related effects will be assessed using 2 × 2 ANOVA (group × time). Differences between variables over time (time effect, from baseline to 3 months) in each group will be evaluated using a paired *t*-test or a non-parametric test. For categorical variables, a chi-squared test will be employed to detect differences. A two-tailed *P* value of <0.05 will be considered to be significant. In addition, differing intervention effects on pulmonary function have been found in previous studies [4, 32, 33], and disease severity may be an important contributor. Therefore, a pre-specified subgroup analysis will be performed to investigate the differences in effectiveness according to disease severity.

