There are several highlights to this study. First, the prescribed pulmonary exercise is a rearrangement of traditional Chinese exercise and targeted to COPD patients. The effects of this prescribed pulmonary exercise on lung function, respiratory muscle strength, exercise capacity, skeletal muscle function, quality of life, and physical activity on stable COPD patients will be evaluated. Second, the role of prescribed pulmonary exercise in improving skeletal muscle function and exercise capacity will be determined by comparing the effects of pulmonary exercise and an elastic band program. Third, the effect of pulmonary exercise combined with exercising with elastic bands in stable COPD patients will be determined, and the effects compared with a single program to determine whether combined exercise can achieve additional beneficial effects. Fourth, the study will apply comprehensive measurements to evaluate skeletal muscle function in patients with COPD, including isokinetic muscle strength testing, surface myoelectricity, 6MWT, and the 30-s arm curl test. Fifth, a sub-analysis will be performed to investigate if the treatment effects differ in patients with different disease severity to enable the optimization of treatment effects for all patients suffering from the troublesome disease. Finally, the study is in strict accordance with CONSORT guidelines, so that the effects of the prescribed pulmonary exercise can be clearly determined.

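### Severity is named as a possible contributor to response but has no term in the stated main model, and the planned severity subgroup analysis is too imprecise to guide treatment

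*Protocol article*

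**What the plan says.** All of this is in the Protocol article.

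- **Sample size.** The calculation covers one overall contrast, control against pulmonary exercise: "The sample size was based on detecting a minimum difference of 54 m in the 6MWT", and it "used a baseline standard deviation of 57 m". The result is that "the minimum sample size per group is 18 to give a total of 72 participants", raised to 22 per group (88 in all) for 20% drop-out. On severity it adds: "The participants will be recruited to achieve a balanced number of patients with different levels of severity of COPD".
- **Design.** "Participants will be randomly assigned to one of four groups according to a random number table generated by computer". The article names no severity factor in the allocation.
- **Participants.** GOLD stages II to IV are eligible.
- **Statistical analysis.** Training effects are assessed by group × time ANOVA. Severity is put forward as a possible reason for the differing pulmonary-function effects of earlier studies, so "a pre-specified subgroup analysis will be performed to investigate the differences in effectiveness according to disease severity". The analysis is not labelled exploratory.
- **Discussion.** The severity sub-analysis is listed among the study's highlights, with the purpose "to enable the optimization of treatment effects for all patients suffering from the troublesome disease".

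**The concern.** The plan treats severity as potentially important in one place and leaves it out of the stated primary model in another. Balancing severity at recruitment determines how many patients of each level enter the trial. It does not by itself determine how they are spread over four arms of 22. If severity affects the change over 3 months, the stated model neither adjusts for a chance difference between arms nor gains precision from a variable already measured at baseline.

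The subgroup analysis has a separate problem. The trial is sized for one two-arm comparison, and splitting each arm by severity leaves few patients per cell. Apparent differences in effect between severity levels could easily be chance, and the Discussion gives them a role in choosing treatment.

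**Working it through.** **1. The plan's own figure.** Inputs from Sample size: difference 54 m, SD 57 m, 80% power, two-sided 5%.

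n per arm = 2 × [57 × (1.960 + 0.842) / 54]² = 17.5, rounded up to 18. This reproduces the stated number (a t-test solution gives 18.5, so 19). Drop-out: 18 × 1.2 = 21.6, so 22 per arm and 88 in all, as stated.

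**2. Cell sizes.** The article does not define the strata, so equal strata are my assumption.

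- Three stages: 72 / (4 × 3) = 6 evaluable and 88 / 12 = 7.3 randomised per arm per stage.
- Two strata: 72 / 8 = 9 evaluable and 88 / 8 = 11 randomised per arm per stratum.

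**3. Effect within a stratum, SD 57 m.** Two-sample t-test, standardised effect 54 / 57 = 0.947.

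- n = 6: power 32%; n = 7: 37%; n = 9: 47%; n = 11: 56%.
- 95% CI half-width = t × 57 × √(2/n): 2.228 × 57 × 0.577 = 73 m at n = 6, and 2.179 × 57 × 0.535 = 66 m at n = 7. Both exceed the 54 m target.

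**4. Difference in effect between two strata, SD 57 m.** This is the quantity the subgroup analysis is about. SE = 57 × √(4/n), and the difference detectable with 80% power is 2.802 × SE.

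- n = 6: SE 46.5 m, detectable 130 m; n = 7: SE 43.1 m, detectable 121 m. Power for a 54 m difference in effect is 21–24%.
- n = 9: SE 38.0 m, detectable 106 m; n = 11: SE 34.4 m, detectable 96 m. Power for 54 m is 29–35%.

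**5. Allowing for the baseline measurement.** The group × time contrast is a comparison of changes, so the relevant SD is 57 × √(2(1 − r)), where r is the baseline-to-3-month correlation. The documents give no r; 0.5 to 0.8 is assumed. At r = 0.5 the SD stays at 57 m.

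| r | SD of change | Strata | Power for 54 m within a stratum | Detectable difference in effect between two strata |
|---|---|---|---|---|
| 0.5 | 57.0 m | three | 32–37% | 121–130 m |
| 0.7 | 44.2 m | three | 48–56% | 94–101 m |
| 0.8 | 36.0 m | three | 65–73% | 76–82 m |
| 0.5 | 57.0 m | two | 47–56% | 96–106 m |
| 0.7 | 44.2 m | two | 68–78% | 75–82 m |
| 0.8 | 36.0 m | two | 85–92% | 61–67 m |

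In the most favourable row, power within a stratum passes 80%. In every row, the detectable difference in effect between strata is larger than the whole 54 m effect for which the trial was sized.

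**The case against.** A reader might infer more than the article supports, in four ways.

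*That the allocation list is unstratified and the arms will be out of balance.* The article does not say this. A computer-generated table is compatible with strata or blocks, the recruitment sentence could be meant as balance across arms, and a journal article commonly leaves such details to the full protocol. If the list were unstratified, with stages split 29/29/30, simulation gives about a 32% chance that control and pulmonary exercise differ by 5 or more patients in some stage. That figure is conditional and is not part of the finding. What stands is that recruitment, the only mechanism the article names, does not by itself balance arms.

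*That severity confounds the main comparison.* This is too strong. Chance imbalance under randomisation is not bias in expectation. The group × time contrast also removes stable baseline differences in walking distance and spirometry. Only severity-related differences in change remain, so adjustment is a matter of precision and of guarding against chance imbalance.

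*That the plan will run separate tests in three stages with 6–7 patients per arm.* Neither the tests nor the strata are specified. The wording fits an interaction analysis, and details may sit in an analysis plan. Hence the ranges above for two strata and for several correlations.

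*That the protocol makes a confirmatory subgroup claim.* It states an aim in a list of highlights, and its limitations paragraph asks for multi-centre confirmation. Underpowered subgroup analyses are common and acceptable when labelled exploratory. This one carries no such label and is given a treatment-optimising purpose. That part of the concern stands.

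**Conclusion.** The point holds in a limited form. The protocol regards severity as a possible contributor to response, omits it from the stated main model, and gives a treatment-guiding purpose to a subgroup analysis that cannot supply it.

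The size depends on assumptions the documents do not settle: equal strata, their number, the protocol's 57 m SD, and the baseline correlation. With three stages, power for 54 m within a stage is about 32–37% if the baseline gives no gain, rising to about 65–73% at a correlation of 0.8. The detectable difference in effect between stages is about 76–130 m. Two strata with a high correlation would give adequate power within each stratum, but still could not reliably detect a 54 m difference in effect between them (61–67 m detectable). The conclusion that severity-specific guidance is out of reach therefore survives the whole range examined. The documents do not support a finding that the randomisation is defective or the main comparison biased.

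**What to change.** 1. **Main model.** Add baseline FEV1 %predicted as a covariate. In a repeated-measures group × time model it should enter together with its product with time, because a term constant over time leaves the complete-data change contrast unaltered. In an analysis of 3-month values or changes, an ordinary covariate is enough.
2. **Severity analysis.** Make it a single arm × continuous baseline FEV1 %predicted interaction on the 3-month change, reported with a confidence interval and labelled exploratory. This avoids undefined cut-points and thin cells. It assumes a roughly linear relation and will not make the analysis well powered. Its power cannot be computed here, because the documents do not give the expected spread of FEV1 %predicted in this trial.
3. **Discussion.** Reword the highlight to say that the analysis explores whether effects vary with severity and generates hypotheses, without promising severity-specific treatment guidance.
4. **Clarification only.** Ask whether the allocation list is stratified by severity, and state the answer. Changing the envelopes during recruitment is not recommended: in an open-label, single-centre trial, small fixed blocks over four arms would make late assignments in a block predictable.

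The cost is an extra model term, a wording change and a more modest stated aim. No new measurements or patients are needed.
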